   **VITAL SIGNS:**

   | Temperature: °C Heart rate: beats per min Respiratory rate: breaths/min  BP: mmHg Hydration Status: Sternal capillary refill time >2seconds ☐Yes ☐No GCS: Oxygen saturation (SPO2): % on ☐room air ☐oxygen therapy ☐Unknown |
   | --- |

   **Standard Treatment for Severe cases (ST_NS_):**

   Strict Isolation: ☐Yes ☐No ☐Unk

   Standard Precautions (Hand hygiene, Cough Etiquette, Wear surgical mask): ☐Yes ☐No ☐Unk

   Nutrition: ☐Enteral ☐Parenteral ☐Unk

   Supportive Pharmacotherapy (Antipyretic, Antiallergic, Cough Suppressant if any with days and frequency)

   ______________________________________________

   _______________________________________________

   ______________________________________________

   Treatment of Comorbid Diseases(to mention condition and treatment given)

   Antibiotic agents for other associated infections (according to 2019 ATS/IDSA guidelines for non-ICU and ICU patients)

   ______________________________________________

   _______________________________________________

   ______________________________________________

   Oseltamivir (for patient who are tested positive for H1N1)

   Total number of days received:

   Dosage and Frequency:

   Treatment Group:

   ☐Treatment Arm: A (Hydroxychloroquine 400mg BD on day1 followed by 400 mg once daily for 10 days + Standard Treatment ST_s_)

   ☐Treatment Arm: B (Lopinavir(400mg) + Ritonavir(100mg) two tablets twice daily for 14 days+STs)

   ☐Treatment Arm: C (Lopinavir(400mg) + Ritonavir (100mg)+ Ribavirin)

   **CLINICAL FEATURES** (Unk = Unknown)

   | Cough and sputum production  Sore throat  Chest pain  Shortness of breath  Confusion | ☐Yes ☐No ☐Unk  ☐Yes ☐No ☐Unk  ☐Yes ☐No ☐Unk  ☐Yes ☐No ☐Unk  ☐Yes ☐No ☐Unk | Seizures  Vomiting  Nausea  Diarrhoea  Conjunctivitis  Myalgia  Other, specify_______ | ☐Yes ☐No ☐Unk  ☐Yes ☐No ☐Unk  ☐Yes ☐No ☐Unk  ☐Yes ☐No ☐Unk  ☐Yes ☐No ☐Unk  ☐Yes ☐No ☐Unk  ☐Yes ☐No ☐Unk |
   | --- | --- | --- | --- |

   **LABORATORY RESULTS ON FOLLOW UP** (*record units if different from those listed)

   | Parameter | Value | Not done | Parameter | Value | Not done |
   | --- | --- | --- | --- | --- | --- |
   | Haemoglobin (g/L) |  |  | Urine R/M (significant if any) |  |  |
   | WBC count (x109/L |  |  | Sodium (mEq/L |  |  |
   | Haematocrit (%) |  |  | Potassium (mEq/L) |  |  |
   | Platelets (x109/L) |  |  | Calcium(mg/dL) |  |  |
   | APTT/PT/INR |  |  | Lactate (mg/dL) |  |  |
   | Total bilirubin (mg/dL) |  |  | Procalcitonin (ng/mL) |  |  |
   | Direct bilirubin (mg/dL) |  |  | CRP (mg/L) |  |  |
   | Albumin (g/dl) |  |  | LDH (U/L) |  |  |
   | Globulin (g/dl) |  |  | Creatine kinase (U/L) |  |  |
   | SGOT/SGPT (U/L) |  |  | Troponin (ng/mL) |  |  |
   | Urea (mg/dL) |  |  | ESR (mm/hr) |  |  |
   | Creatinine (mg/dL) |  |  | D-dimer (mg/L) |  |  |
   | Others |  |  |  |  |  |

   **Influenza virus**: ☐Positive ☐Negative ☐Not done If positive, type ______________ **Coronavirus:** ☐Positive ☐Negative ☐Not done If positive: ☐MERS-CoV ☐SARS-CoV-2 ☐Other **Other respiratory pathogen**: ☐Positive ☐Negative ☐Not done If positive, specify:____________

   **Other pathogen of public health interest detected**: If yes, specify: __________________________

   **Radiological Investigations** (if performed):

   Chest X Ray/CT Performed (report):

   Ultrasonography:

   Others

   **SUPPORTIVE CARE** Is the patient CURRENTLY receiving any of the following?

   | ICU or High Dependency Unit admission? Yes No Unknown  Date of ICU/HDU admission [__][__]/[__][__]/[__][__][__][__] , ☐Unknown  ICU/HDU discharge date [__][__]/[__][__]/[__][__][__][__],☐Not discharged yet ☐Unknown  Oxygen therapy? ☐Yes ☐No ☐Unknown If yes, complete all below:  O2 flow volume: ☐1-5 L/min ☐6-10 L/min ☐11-15 L/min ☐>15 L/min ☐Unknown  Source of oxygen: ☐Piped ☐Cylinder ☐Concentrator ☐Unknown  Interface: ☐Nasal prongs ☐HF nasal cannula ☐Mask ☐Mask with reservoir ☐CPAP/NIV mask ☐Unknown  Non-invasive ventilation? (e.g. BIPAP, CPAP) ☐Yes ☐No ☐Unknown  Invasive ventilation (Any)? ☐Yes ☐No ☐Unknown  Inotropes/vasopressors? ☐Yes ☐No ☐Unknown  Prone position? ☐Yes ☐No ☐Unknown  Renal replacement therapy (RRT) or dialysis? ☐Yes ☐No ☐Unknown |
   | --- |

   **Previous Treatment Regime** (If any-to specify group with duaration):

   ☐Non-Severe Treatment arms (NS-group): Treatment Arm-A:___________________________

   ☐Non-Severe Treatment arms (NS-group): Treatment Arm-B:___________________________

   ☐Severe Treatment arms (S-group): Treatment Arm-A:___________________________

   ☐Severe Treatment arms (S-group): Treatment Arm-B:___________________________

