|  | Title of the project: **“Safety and efficacy of antiviral therapy alone or in combination in symptomatic patients of Covid-19 infection - a randomised controlled trial (SEV-Covid Trial)”** |
| --- | --- |
| (a) | Aim: To assess the safety and efficacy of Antiviral Therapy In Symptomatic Patients of COVID-19 Infection |
| (b) | Objectives:   1. To compare the safety and efficacy of Hydroxychloroquine with Ribavirin and standard treatment in patients of non-severe COVID-19 infection 2. To compare the safety and efficacy of standard treatment, Lopinavir-ritonavir with Ribavarin, and Hydroxychloroquine with Ribavirin in patients of severe COVID-19 infection |
| (c) | **Justification for study**: COVID 19 infection had become a pandemic. The presentation of the disease is highly variable. The treatment options for the disease are limited at present. For non-severe patient’s supportive treatment forms the mainstay of management. Various regimens have been tried in critically ill patients. Hydroxychloroquine, Lopinavir-ritonavir combination has been tried in clinical trials with limited success. The present study is planned to explore the combination of the above drugs with Ribavirin in different categories of COVID-19 infection. |
| (d) | **Scope of the Project**: The present study will evaluate the therapeutic potential of Hydroxychloroquine and Lopinavir-ritonavir in combination with Ribavirin in symptomatic cases of COVID-19 infection in a tertiary care hospital in India |

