| (e) | Details of procedure and methodology proposed to be used (300 words) including description of the potential risks and benefits, exclusion and Inclusion criteria outcome measures, statistical analysis:  ***Patient population:*** *Covid-19 positive symptomatic cases either non-severe or severe category*  ***Intervention:*** *Two therapeutic interventions for non-severe category and three for severe category as described below*  ***Comparator:*** *Parallel arm design, compared among other interventional arm in same category*  ***Outcomes:*** *Clinical and laboratory improvements in 72 hours of treatment*  **Patient population-**  Patients diagnosed with SARS-CoV-2 infection after positive reverse-transcriptase–polymerase chain reaction (RT-PCR) assay.  **Inclusion criteria:**   1. Age ≥18 years at time of participation in the study 2. Laboratory (RT-PCR) confirmed infection with SARS-CoV-2 3. Symptomatic (severe or non-severe) Covid-19 disease 4. Willingness of study participant to accept randomization to any assigned treatment arm   **Exclusion criteria:**   1. Use of medications that are contraindicated with Lopinavir/Ritonavir, Hydroxychloroquine/Chloroquine, or Ribavirin and that cannot be replaced or stopped 2. Patient already on antiretroviral therapy with Lopinavir-Ritonavir based regimen or on Hydroxychloroquine/Chloroquine or on Ribavirin 3. Any known contraindication to test drugs such as retinopathy and QT prolongation 4. Known allergic reaction or inability to delivery oraly to Lopinavir-ritonavir, Hydroxychloroquine/ Chloroquine, Ribavarin 5. Pregnant or breastfeeding females 6. Receipt of any experimental treatment for 2019-nCoV (off-label, compassionate use, or trial related) within 30 days prior to participation in the present study or want to participate after enrolment   **Potential benefits:**   1. All those who participate in the trial will benefit from possible effective treatment for COVID-19 infection 2. The study will highlight the therapeutic options in management of the symptomatic patients of COVID-19 infection   **Potential risks:**  The present study will be conducted on symptomatic patients of COVID-19 attending AIIMS Rishikesh. The patients will be categorised based on severity and treatment will be allocated accordingly.  Adverse drug reactions, though not frequent may be associated with the treatment. Proper supportive management will be given to the patients at the institute.  **Methodology**:  **Flow Diagram**  Patients of COVID-19 infection - After confirmation by RT-PCR at AIIMS, Rishikesh  Screening for inclusion in trial Enrolment Excluded  ♦  Not meeting inclusion criteria  ♦  Declined to participate  ♦  Other reasons  Categorisation based on severity of patient  **SEVERE group**  **NON-SEVERE group**  Randomisation to treatment arm:  **A. Standard Treatment (ST-S)**  **B. Hydroxychloroquine + Ribavirin + ST-S**  **C. Lopinavir+ Ritonavir + Ribavirin + ST-S**  Randomisation to treatment arm:   1. **Standard Treatment (ST-NS)** 2. **Hydroxychloroquine + Ribavirin + ST-NS**  RandomisationAllocation Monitor progress of patient in 72 hours Follow-Up Patient improve- continue same treatment  Clinical evaluation- @72 hours  Improve - Continue same treatment  Progress – achieved end point and Shift to institute protocol for further treatment  Patient do not improve/ Signs of severe disease  Shift to **SEVERE group** treatment arms after randomization with new consent Analysis Analysis  **Total duration of observation**:  28 days from the time of enrolment into the study OR till patient is discharged or death whichever is longer  **Design:** Open label, Parallel arm design, stratified randomised controlled trial:  Patients will be screened for the study after diagnosis of COVID-19 infection by Microbiology team. Patients will be categorised as non-severe or severe based on predefined criteria. The patient will be enrolled in the study after a written informed consent. Since it is an exploratory trial as COVID-19 being a new disease, all patients who came under the purview of the inclusion criteria within the study period and who have consented for the study will be included. Clinical evaluations will be done by a separate investigator. Blinding will not be performed but dynamic randomization will be done. Patients will be followed up for a period of 28 days from the day of enrolment.  At the time of enrolment, demographic information will be collected from participants, and relevant data on their medical histories, comorbidities, and risk factors for severe COVID-19. It will be documented along with investigations including CBC, ECG, LFT, RFT, G6PD status.  The patients will be categorised as severe based on the following criteria:   - Confirmed pneumonia on chest imaging, SPo2 <93%, Pao_2_:Fio_2_ <300 mg Hg - Respiratory failure (need of mechanical ventilation) - Septic shock - Multiple (>2) organ dysfunction syndrome (MODS) - Liver disease (Child Pugh score ≥ C, AST>5 times upper limit) - Patients with known renal impairment (estimated glomerular filtration rate ≤30 mL/min/1.73 m2) or receiving continuous renal replacement therapy, haemodialysis, peritoneal dialysis - Other single organ failure (e.g. heart, pancreas, etc) if specific definition meets   Non-severe category includes mild and moderate disease severity category other than severe ones.  **Treatment Schedule**  **Non-severe Treatment arms (NS-group):**   \| **Treatment Arm** \| **Drug** \| \| --- \| --- \| \| A \| Standard Treatment (ST_NS_) \| \| B \| Hydroxychloroquine 400 mg twice on first day followed by 400 mg per oral daily for 10 days + Ribavirin (2.4 g orally as a loading dose followed by 1.2 g orally every 12 hours) for 10 days + Standard Treatment (ST_NS_) ^6^ \|   **Standard Treatment for non-severe cases (ST_NS_):**   1. Strict Isolation 2. Standard Precautions (Hand hygiene, Cough Etiquette, Wear surgical mask) 3. Hydration 4. Proper Nutrition 5. Supportive Pharmacotherapy (Antipyretic, Antiallergic, Cough Suppressant) 6. Treatment of Comorbid Diseases 7. Oseltamivir (75 mg BD) for patient who are tested positive for H1N1   If the patient improves clinically the same treatment will be continued. If the patient do-not improve or shows sign of severity (mentioned above) the patient will be shifted to the severity arm (S-group) of the clinical trial and again randomization will be done and enrolled after new consent only for severe group. However, if intervention falls on HCQ arm, then it will be taken as end point reached and shifted to institute treatment protocol for further management.  **Severe group Treatment arms (S-group):**   \| **Treatment Arm** \| **Drug** \| \| --- \| --- \| \| A \| Standard Treatment (ST_s_) \| \| B \| Hydroxychloroquine 400mg BD on day1 followed by 400 mg once daily + Ribavirin (2.4 g orally as a loading dose followed by 1.2 g orally every 12 hours) for 10 days + Standard Treatment (ST_s_) \| \| C \| Lopinavir(400mg) + Ritonavir (100mg) two tablets twice daily+ Ribavirin (2.4 g orally as a loading dose followed by 1.2 g orally every 12 hours) for 10 days + Standard Treatment (ST_s_)^6^ \|   **Standard Treatment for severe patients: (ST_s_)**   1. Strict Isolation 2. Standard Precautions (Hand hygiene, Cough Etiquette, Wear surgical mask) 3. Fluid Therapy 4. Supportive Pharmacotherapy (Antipyretic, Antiallergic, Cough Suppressant) 5. Oxygen supplementation (As required) 6. Invasive ventilation (As required) 7. Antibiotic agents for other associated infections (according to 2019 ATS/IDSA guidelines for non-ICU and ICU patients) 8. Vasopressor support 9. Renal-replacement therapy 10. Treatment of Comorbid Diseases 11. Oseltamivir (75 mg BD) for patient who are tested positive for H1N1   Patients will be assessed for clinical and laboratory improvements in 72 hours of treatment. In case the patient does not respond to the current treatment regimen the patient will be shifted to institute protocol for current practice of treatment.  **Timelines of investigations: Repeated at 72hrs interval**   \| Investigations \| Baseline \| Next 72hrs \| \| --- \| --- \| --- \| \| CBC \| **✔** \|  \| \| LFT \| **✔** \|  \| \| KFT \| **✔** \|  \| \| HBA1C and Blood sugar \| **✔** \|  \| \| RT-PCR for SARS-Cov-2 (until 24hrs apart twice negative) \| **✔** \|  \| \| PT/INR \| **✔** \|  \| \| Serum Electrolytes \| **✔** \|  \| \| ABG \| **✔** \|  \| \| Chest Xray \| **✔** \|  \| \| ECG \| **✔** \|  \| \| Other organ markers as per involvement \| **✔** \|  \|     **Dose Modifications:**  If any serious adverse event is recorded, the participant will be withdrawn from the trial and management will be done accordingly as per institute policy.  **Recording adverse events:**  All adverse events will be recorded in the medical records in the first instance. All adverse events will be recorded with clinical symptoms and accompanied with a simple, brief description of the event, including dates as appropriate. Each adverse event will be assessed for severity, causality, seriousness and expectedness and informed to IEC within 24hours.  **Discontinuation/withdrawal of participants:**  A participant may be withdrawn from trial treatment whenever continued participation is no longer in the participant’s best interests, but the reasons for doing so must be recorded.  Reasons for discontinuing treatment may include:   1. Unacceptable drug toxicity 2. Development of progressive disease 3. Patients withdrawing consent to further trial treatment   **Endpoints:**  **Primary endpoints:**   1. Time to Clinical recovery (TTCR)    - TTCR is defined as the time (in hours) from initiation of study treatment (active or placebo) until normalisation of fever, respiratory rate, and oxygen saturation, and alleviation of cough, sustained for at least 72 hours.    - Normalisation and alleviation criteria: 2. Fever - ≤36.9°C or -axilla, ≤37.2 °C oral 3. Respiratory rate - ≤24/minute on room air 4. Oxygen saturation - >94% on room air 5. Cough- mild or absent on a patient reported scale of severe, moderate, mild, absent 6. Time to SARS-CoV-2 RT-PCR negative in upper respiratory tract specimen 7. Time to laboratory recovery of each organ involvement   **Secondary Endpoints:**   1. All causes mortality 2. Frequency of respiratory progression  - Defined as SPO2≤ 94% on room air or PaO2/FiO2 <300mmHg and requirement for supplemental oxygen or more advanced ventilator support.  1. Time to defervescence (in those with fever at enrolment) 2. Frequency of requirement for supplemental oxygen or non-invasive ventilation 3. Frequency of requirement for mechanical ventilation 4. Frequency of serious adverse events as per AIDS table grade of severity   **Statistical analysis**:  All COVID-19 positive patients will be included in the study after informed consent. Since it is an exploratory trial as COVID-19 being a new disease, all patients who came under the purview of the inclusion criteria within the study period and who have consented for the study will be included. Data will be described as mean+ SD for most of the parameters. Comparisons of the descriptive variables of the two arms will be performed using the Wilcoxon rank sum test for continuous variables and the chi-square or Fisher’s exact test for categorical variables. Primary analysis will include all patients (Intention to treat) and sub-group populations (per-protocol).  **Ethical clearance:**  The present study deals with a new infectious disease which has no definite treatment. Current therapy is based on symptomatic treatment. The present study explores the possibilities of new drugs in SARS-CoV-2 infection. The study will be conducted after IEC approval. Written informed consent will be taken from all participants.  **Safety Outcomes**  Safety outcomes will be determined according to the division of AIDS table for grading severity of adult adverse events (<https://rsc.niaid.nih.gov/clinical-research-sites/daids-adverse-event-grading-tables>), with specific focus on the events of gastrointestinal tract, arrhythmias, myopathies. In case of serious ADRs including death, compensation will be given as per institute protocol. |

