**Day of Hospitalization: _______________ Date of follow-up: [__][__]/[__][__]/[__][__][__][__]**

**VITAL SIGNS:**

| Temperature: °C Heart rate: beats per min Respiratory rate: breaths/min  BP: mmHg Hydration Status: Sternal capillary refill time >2seconds ☐Yes ☐No GCS:  Oxygen saturation (SPO2): % on ☐ room air ☐oxygen therapy ☐Unknown |
| --- |

Standard Treatment for non-severe cases (ST_NS_):

1. Strict Isolation: ☐Yes ☐No ☐Unk
2. Standard Precautions (Hand hygiene, Cough Etiquette, Wear surgical mask): ☐Yes ☐No ☐Unk
3. Nutrition: ☐Enteral ☐Parenteral ☐Unk
4. Supportive Pharmacotherapy (Antipyretic, Antiallergic, Cough Suppressant if any with days and frequency)

- ______________________________________________
- _______________________________________________
- ______________________________________________

1. Treatment of Comorbid Diseases(to mention condition and treatment given)
2. Oseltamivir (for patient who are tested positive for H1N1)

- Total number of days received:
- Dosage and Frequency:

1. Treatment Group:

☐Treatment Arm: A (Standard Treatment-ST_NS_)

☐Treatment Arm: B (Hydroxychloroquine 400 mg twice on first day followed by 400 mg per oral daily for 10 days + Standard Treatment -ST_NS_) ^^[[2]](#endnote-1)^^

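### Three of the five treatment-arm boxes on the case report form contradict the randomised arm of the same letter, and two of the three severe arms have no correctly described box

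*Protocol*

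**What the plan says.** **Methods.** Protocol item (b), objective 2, names the three severe regimens: "To compare the safety and efficacy of standard treatment, Lopinavir-ritonavir with Ribavarin, and Hydroxychloroquine with Ribavirin in patients of severe COVID-19 infection". The flow diagram in item (e) gives them letters: "A. Standard Treatment (ST-S", "B. Hydroxychloroquine + Ribavirin + ST-S" and "C. Lopinavir+ Ritonavir + Ribavirin + ST-S". The severe table under Treatment Schedule uses the same letters and drugs. For the non-severe group, arm A is standard treatment and arm B opens "Hydroxychloroquine 400 mg twice on first day followed by 400 mg per oral daily for 10 days + Ribavirin", with standard treatment added.

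**CRF, non-severe form, Treatment Group.** Box A is standard treatment. The other box is "Treatment Arm: B (Hydroxychloroquine 400 mg twice on first day followed by 400 mg per oral daily for 10 days + Standard Treatment", and ribavirin does not appear in it.

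**CRF, severe form, Treatment Group.** The first box is "Treatment Arm: A (Hydroxychloroquine 400mg BD on day1 followed by 400 mg once daily for 10 days + Standard Treatment". Box B is lopinavir-ritonavir for 14 days plus standard treatment. Box C is lopinavir-ritonavir plus ribavirin, with no frequency, duration, ribavirin dose or mention of standard treatment.

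**Duration.** In the Treatment Schedule, severe arm C reads, from the lopinavir-ritonavir frequency onward, "two tablets twice daily+ Ribavirin (2.4 g orally as a loading dose followed by 1.2 g orally every 12 hours) for 10 days".

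**The concern.** The methods define the arms consistently, but the form on which the arm is recorded does not follow them. Ticked by letter, a severe control is labelled as receiving hydroxychloroquine, and a hydroxychloroquine plus ribavirin patient is labelled as receiving lopinavir-ritonavir. Ticked by description, a severe control has no matching box, and the nearest box for a hydroxychloroquine plus ribavirin patient is A, the only severe box that names hydroxychloroquine. If practice varies between staff, box A could hold both groups, and the form alone could not separate them.

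The trial is open label, so staff know the drugs and either way of ticking is plausible. On the follow-up forms, no field other than the Treatment Group box names these study drugs. What is at stake is any comparison by treatment group, including safety, that takes its arm from the CRF.

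**Working it through.** The plan states no figure on this point, so the check sets each CRF box beside the randomised arm of the same letter. The arms come from the flow diagram and the Treatment Schedule tables in item (e). The boxes come from the Treatment Group item on the two CRF follow-up forms. ST = standard treatment, HCQ = hydroxychloroquine, RBV = ribavirin, LPV/r = lopinavir-ritonavir, NS = non-severe, S = severe.

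| Arm | Methods | CRF box | Result |
| --- | --- | --- | --- |
| NS-A | ST | ST | agrees |
| NS-B | HCQ + RBV + ST | HCQ + ST | RBV omitted |
| S-A | ST | HCQ + ST | an antiviral printed for the control arm |
| S-B | HCQ + RBV + ST | LPV/r 14 days + ST | different antivirals |
| S-C | LPV/r + RBV + ST | LPV/r + RBV | same drugs, label abbreviated |

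Counts:

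- Boxes that contradict the arm of the same letter: NS-B, S-A and S-B = 3 of 5. S-C is incomplete but not contradictory, so it is not counted.
- Kind of error: S-A and S-B print antivirals that are not those of the arm (2 of 5). NS-B leaves out one drug (1 of 5).
- Arms not correctly described in any box on their form: S-A and S-B, 2 of 3 severe; NS-B, 1 of 2 non-severe; 3 of 5 overall.
- Ribavirin: part of 3 of 5 arms (NS-B, S-B, S-C), printed in 1 of 5 boxes (S-C).

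The errors differ in consequence. The non-severe form has only two boxes, one of them plain standard treatment, so an NS-B patient can still be identified although the regimen is misdescribed. The severe form offers no such way out for A and B.

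Durations were checked separately, because copying the methods onto the form settles them only if the methods are clear. In NS-B, hydroxychloroquine and ribavirin each carry their own 10 days. In S-C, a single 10 days stands after ribavirin, and in S-B a single 10 days likewise stands after ribavirin and not after hydroxychloroquine. Two readings are possible:

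1. The 10 days covers the whole regimen. The CRF's 14 days of lopinavir-ritonavir then exceeds it by 14 − 10 = 4 days.
2. The 10 days covers ribavirin only. The methods then give no duration for lopinavir-ritonavir in S-C or for hydroxychloroquine in S-B. The CRF's 14 days for lopinavir-ritonavir, and on the severe form its 10 days for hydroxychloroquine, are the only figures stated.

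The protocol does not decide between them.

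**The case against.** The strongest reply is that the box is an allocation label and not a dosing record. Every severe arm still has its letter, the methods are consistent, and the intention-to-treat analysis can take the arm from the randomisation record. The opening pages of the CRF are not in the text at hand, so allocation may also be recorded there. All of this stands. It limits the harm but does not make the printed descriptions right.

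Some stronger readings are tempting but are not supported:

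- A reader might infer that the primary analysis will be wrong. The protocol does not say that the analysis arm is taken from this box, so misclassification is a risk and not a certainty.
- A reader might infer that per-protocol membership is lost. The follow-up forms have no study-drug adherence field, so treatment received would need other records even with perfect labels.
- A reader might infer that adverse events will be misattributed because the log has no column for arm or drug. The protocol requires a causality assessment of each event, and a missing column does not show misattribution.
- The severe form's list of previous regimens has severe A and B but not C. That looks like a lost arm, but the methods never move a severe patient to another severe arm. The A and B lines may simply be surplus.
- A reader might infer that the 14 days is a plain error to be deleted. On the second reading above, it may be the intended lopinavir-ritonavir duration.
- A worsening non-severe patient whose new allocation is the hydroxychloroquine arm is treated as having reached the end point. One might expect the conflicting letters to misdirect that rule, but it names the drug and not a letter.

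**Conclusion.** The inconsistency is real. Three of five boxes contradict the arm of the same letter, and two of three severe arms, the control among them, have no correctly described box. The arm recorded on the CRF should not be relied on for treatment-group or safety comparisons unless it is reconciled with the randomisation record. This should be fixed, but it is an internal inconsistency between form and methods and not a fault in the design.

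The conclusion assumes that the methods state the intended arms, which the objectives support, and that a usable randomisation record is kept. It does not assume that any patient was misrecorded or given the regimen printed on the form. The intended durations of lopinavir-ritonavir in severe C and hydroxychloroquine in severe B remain open.

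**What to change.** Reissue the CRF with the methods' arms under the same letters:

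- NS-A: standard treatment
- NS-B: hydroxychloroquine + ribavirin + standard treatment
- S-A: standard treatment
- S-B: hydroxychloroquine + ribavirin + standard treatment
- S-C: lopinavir-ritonavir + ribavirin + standard treatment

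State the lopinavir-ritonavir duration in S-C and the hydroxychloroquine duration in S-B explicitly, and make the treatment table and the CRF agree. The investigator has to supply the intended figures, since neither copying the table nor deleting the 14 days settles them.

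Take the analysis arm from the randomisation record, and check the arm on every form already completed against it.

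The cost is a form reissue and a short amendment, plus the re-verification of completed forms. No extra patients or procedures are needed.

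### The severe follow-up form records respiratory support only as current status, so support that starts and ends between forms may be missed by the 'frequency of requirement' endpoints

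*Protocol*

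**What the plan says.** The Secondary Endpoints, in item (e) of the protocol's brief description of the proposal, include "Frequency of requirement for supplemental oxygen or non-invasive ventilation" and "Frequency of requirement for mechanical ventilation". Observation lasts 28 days from enrolment, or until discharge or death if that is longer.

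The Supportive Care block of the severe follow-up form opens with "Is the patient CURRENTLY receiving any of the following". Its respiratory items are:

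- "Oxygen therapy? ☐Yes ☐No ☐Unknown If yes, complete all below" (the details asked for are flow, source and interface)
- "Non-invasive ventilation? (e.g. BIPAP, CPAP) ☐Yes ☐No ☐Unknown"
- "Invasive ventilation (Any)? ☐Yes ☐No ☐Unknown"

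None of the three has a date. The only dated item in the block is the ICU/HDU stay ("Date of ICU/HDU admission", with a discharge date). The Outcomes block that follows lists clinical recovery, time to a negative RT-PCR, time to defervescence and serious adverse events. It does not ask whether oxygen, NIV or ventilation was ever required.

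The protocol does not say how often the follow-up form is completed. Investigations are "Repeated at 72hrs interval", and the flow diagram places a clinical evaluation at 72 hours.

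**The concern.** The endpoints and the form measure different things. A frequency of requirement over at least 28 days is most naturally a cumulative quantity: did this patient need support at any time? A series of current-status questions gives point prevalence on the form dates. The two agree only when every episode of support overlaps at least one form.

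The same question is suitable on the admission form, where present status is what is wanted. On a follow-up form it leaves the time between forms unobserved. A patient intubated after one form and extubated, or dead, before the next is correctly ticked No on every form that was completed.

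This could cause two problems. Frequencies are understated in every arm. And because the chance of being missed depends on how long support lasts, arms with the same true frequency but different durations would show different recorded frequencies. A larger sample would not remove that difference, and an analysis plan cannot recover data that the form did not collect.

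**Working it through.** The protocol gives no event rate, sample size or power for these endpoints, so there is no figure of its own to reproduce. The mismatch follows from reading the form against the endpoints. The arithmetic below only illustrates its possible size.

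**Inputs**

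- From the protocol: support is recorded as status on the form date; no dates are recorded for the three respiratory items; 72 hours is the only assessment interval given, and it is not given for the form.
- Assumed: forms every T = 3 days or every T = 1 day; one episode of support per patient, starting after enrolment at a time uniform within a form interval; exponential duration with mean m days; a true ventilation frequency of 30% in each arm.

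**Share of episodes on no form**

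Let U be the time from the start of support to the next form, uniform on (0, T). The episode is missed if it ends before U, which has probability 1 − exp(−U/m). Averaging over U:

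missed share = 1 − (m/T) × (1 − exp(−T/m))

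| Mean duration m (days) | Forms every 3 days | Daily forms |
| --- | --- | --- |
| 2 | 48.2% | 21.3% |
| 3 | 36.8% | 15.0% |
| 5 | 24.8% | 9.4% |
| 8 | 16.6% | 6.0% |
| 10 | 13.6% | 4.8% |

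Example, m = 3 and T = 3: 1 − (3/3) × (1 − exp(−1)) = 0.368. Simulation agrees with the formula.

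**Effect on a comparison if duration differs by arm**

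Take a true frequency of 30% in both arms, with mean duration 3 days in one and 8 days in the other.

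- Forms every 3 days: 0.30 × (1 − 0.368) = 19.0% versus 0.30 × (1 − 0.166) = 25.0%, a spurious difference of about 6 points.
- Daily forms: 0.30 × (1 − 0.150) = 25.5% versus 0.30 × (1 − 0.060) = 28.2%, a spurious difference of about 2.7 points.

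In both cases the arm with shorter episodes looks better. If mean duration is the same in both arms, both frequencies shrink by the same factor, and equal true frequencies stay equal.

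**After the change**

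If each form covers the whole time since the previous one and a closing form covers the last interval, the missed share is zero by design.

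**The case against.** A reader might infer that support between forms is never counted. The documents do not support that. Adverse events go first into the medical records, with dates. The adverse event log has start and end dates, a fatal outcome code and a code for non-drug treatment. The Outcomes block has a free-text line for serious adverse events. Intubation followed by early death is the kind of event likely to appear there, and all patients are treated at one hospital whose charts can be checked. This stands, and it limits the claim to 'may be missed'. It does not close the gap: none of these fields identifies oxygen or ventilation, and the protocol does not name any of them as the source for these endpoints.

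A reader might also infer that forms are 72 hours apart. That interval is stated for investigations and for a clinical evaluation, not for the form. The form's fields for day of hospitalization and date of follow-up fit daily use equally well. So both intervals have to be shown, and the loss under daily forms is much smaller.

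A third tempting reading is that the form favours an arm in which ventilated patients die sooner. In the model only duration matters, so quick weaning is missed just as quick death is. A bias between arms needs a difference in duration, which is an assumption here. Faster death would in any case also show in all-cause mortality, a separate secondary endpoint.

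Finally, the severe category includes low oxygen saturation and the need for mechanical ventilation, and the admission form records support at entry. Many severe patients may already be on oxygen when first seen and would be counted. This stands too: the loss concerns support that starts after enrolment, and is likely to matter less for oxygen than for ventilation.

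**Conclusion.** The concern holds in a limited form. As written, the severe follow-up form collects current status for endpoints that need ever-required status, and no dedicated field covers the time between forms. Episodes that start and end between forms may be missed.

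The size cannot be fixed from the protocol because the form interval is not stated. With mean durations of 2 to 10 days, the illustration gives about 14–48% of episodes missed with 72-hour forms and about 5–21% with daily forms, before any recovery through adverse event records or charts. The spurious difference of about 6 points (72-hour) or 2.7 points (daily) rests wholly on assumed inputs: 30% in both arms, mean durations of 3 versus 8 days, exponential shape and one episode per patient. Its direction is conditional: it favours whichever arm has shorter episodes, for whatever reason.

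The endpoints affected are secondary and the trial calls itself exploratory. The correction is still worth making, because it is cheap and has to be made at data collection.

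**What to change.** On the severe follow-up form:

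- Reword the opening of the Supportive Care block to: *At any time since the last form (or since enrolment), has the patient received …?*
- Add start and stop dates for oxygen, NIV and invasive ventilation, as the block already does for the ICU/HDU stay.
- Require a closing form at death or discharge that covers the interval since the last form.

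In the protocol, state how often the form is completed, and define the two endpoints as any use from enrolment to the end of observation.

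The cost is a few form fields and slightly more chart abstraction. No extra procedures or patients are needed, and no stated sample size changes, because none is stated.
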